**[name]**

**[name]**

**[name]**

**[name]**

**Date: August 1, 2010**

**Sponsor: Canadian Institutes of Health Research**

**1.0 Introduction**

1.1 Background

The Canadian Institutes of Health Research (CIHR) has awarded our project team three years of support for the research project entitled “Optimizing Healthcare Worker Interpandemic Vaccine Uptake in Acute and Long-Term Care”. The goals of this project are to 1) evaluate the use of the Ottawa Influenza Decision Aid (OIDA) as an adjunct to occupational influenza immunization campaigns in acute and long term healthcare organizations; 2) to develop and evaluate the use of a Guide for influenza immunization campaigns including methods to integrate the OIDA into a campaign; and 3) to establish a national knowledge exchange network to improve best practices in influenza immunization among healthcare personnel. We describe here the components of the project involving the implementation and evaluation of the Guide“Successful Influenza Immunization Campaigns in Healthcare Organizations: A Guide for Campaign Planners” to be used by healthcare organizations to plan their seasonal influenza immunization campaign for healthcare personnel.

Keeping nurses, physicians and allied health professionals working during seasonal influenza epidemics is essential. Influenza immunization has been shown to mitigate the adverse health outcomes associated with influenza in the community. When provided to healthcare personnel, influenza vaccine reduces the frequency and severity of nosocomial influenza outbreaks and reduces influenza-associated morbidity and mortality among patients by reducing the transmission of influenza from healthcare personnel to their vulnerable patients (1).

Influenza is one of the leading causes of acute respiratory infection and results in significant increases in average life-years lost, hospital lengths of stay and outpatient clinic visits (2-4), representing an enormous economic burden for many countries (5). Healthcare personnel are at high risk of exposure to influenza as they are exposed in both the community and in the workplace (6). Influenza immunization for healthcare personnel has been shown to reduce patient mortality in long-term care facilities as well as employee absenteeism and financial costs in acute care settings (7-12). The Canadian National Advisory Committee on Immunization (NACI) recommends that influenza immunization campaigns strive to immunize at least 90% of eligible recipients (13). In fact, NACI regards influenza immunization of healthcare personnel with direct patient care responsibilities as an essential component of the standard of care for the protection of patients and the refusal of healthcare personnel without contraindications to receive influenza vaccine as a failure in their duty of care to patients. Despite national recommendations and proven effectiveness, influenza immunization coverage rates among healthcare personnel remain below targeted levels (13).

1.2 Poor Uptake of Influenza Vaccine by Healthcare Personnel

Despite abundant evidence of the safety and efficacy of the influenza vaccine, immunization rates among healthcare personnel in hospital and long-term settings remain well below the public health target of 90%. Current initiatives targeted at increasing healthcare personnel immunization rates are having limited success with healthcare personnel immunization rates as low as 2%, but averaging 40% - 60% in most healthcare facilities being reported (1,2,12).

1.3 Development of the Guide: “Successful Influenza Immunization Campaigns for Healthcare Personnel - A Guide for Campaign Planners”

Healthcare organizations have a wide variety of approaches to the immunization of their workers. Each influenza season, healthcare planners devote time and effort to encourage staff immunization through a seasonal influenza immunization campaign. While the majority of healthcare organizations are committed to vaccinating their personnel, they, however, work in isolation, with few resources and limited evidence to inform the development and running of a successful immunization campaign. Moreover, there are almost no additional resources available and often few opportunities to share ideas, ask questions, or boast successes with other organizations (14).

During the first year of the project team’s grant (2008-2009), we conducted a series of consultation meetings in Ontario and Nova Scotia with five long-term care homes and three acute care hospitals. We spoke to the influenza campaign teams typically comprising of occupational health and infection control leaders as well as other managers. The results of these consultation meetings led to the first draft of the Guide: “Successful Influenza Immunization Campaigns for Healthcare Personnel: A Guide for Campaign Planners” (see Appendix 1).

The goal of this study is to validate the Guide and additional web-based “grab and go” tools (the Toolkit).

The Guide is structured to facilitate the use of the evidence-based research on strategies to increase immunization rates by healthcare planners. It also introduces ways to incorporate the Ottawa Influenza Decision Aid (OIDA, another tool in produced by the project team) into their campaign. The Guide is based on the following sources of information: 1) Systematic review of literature on interventions to increase healthcare personnel immunization rates (15); 2) ideas from consultation meetings with campaign organizers, 3) experiences of organizations implementing the OIDA in 2008-2009, 4) results from the OIDA pilot studies, 5) input from Occupational Health and Infection Control practitioners working closely with the project team and 6) additional research by team members on specific topics within the Guide.

In 2009, this Guide was pilot-tested and updated based on the feedback that was received. During the 2009-2010 influenza campaign, despite the impact of H1N1, sixteen healthcare organizations agreed to use and evaluate the Guide. Those who used the Guide during the pilot test reported that the Guide had a positive impact on their program, with 100% indicating they would recommend it to other organizations and 90% stating they made changes to their organization’s influenza immunization campaign for their healthcare personnel based on the information contained in the Guide.

Following completion of the study, we will work with partner organizations to make these tools available to all Canadian healthcare organizations.

Comments received from users of Version One of the Guide:

“Provides a structured and planned approach to ensure everything is covered”

“Helped us to approach campaign in a planned way”

“Provided pre-planning ideas that resulted in better communication and dialogue from employees”

“I felt better prepared to research new resources and build on old ones”

| **What they learned …** |
| --- |
| - Importance of providing education to employees (i.e. risks, benefits of flu shot) - Necessity of identifying resources required - Importance of good communication plan - Importance of pre-planning and post-campaign evaluation and feedback - Incentives - Calculation of statistics - Getting involvement from others - Use of informed declination - Increase role of communications and human resources at all stages of campaign - More than 1-2 components (methods) used to increase participation - The need to review policies and procedures - Identification of barriers and how to overcome them - Identification of what you can improve as a facility and an organization - Validated and clarified what we had in place |
| **What they liked …** |
| - Checklist at front is excellent - Self-explanatory – clean and concise - Use of expanded team - SWOT (Strengths, Weakness, Opportunities, Threats) - A lot of new things, planning guide very helpful - Declination form - OIDA - Influenza season – approach, making it sensible and evaluating what I could do to improve - Very helpful (especially the section on identifying your team) |

During the 2010–2011 and the 2011-2012 seasonal influenza immunization campaigns, we will recruit a minimum of 46 healthcare organizations to either conduct their campaigns as usual or to use the Guide and the Toolkit. At the end of the campaign season we will evaluate the impact of the Guide and web-based tool and assess whether there were changes in immunization rates within each organization and/or if there were significant changes in the management of the campaigns across organizations.

Successful Influenza Immunization Campaigns in Healthcare Organizations: A Guide for Campaign Planners (the Guide) is designed for:

- Healthcare organizations committed to improving immunization rates
- The person or team responsible for implementing the campaign within their organization (or component of a healthcare organization)

The evidence-based Guide includes:

- Checklists
- Simple, easy-to-use framework
- Electronic templates (in the Toolkit) that can be customized
- Interactive web-based tools

1.4 Research Question

Among healthcare organizations who conduct Seasonal Influenza Immunization Campaigns, does use of the Guide impact the effectiveness of these campaigns as measured by change of healthcare personnel immunization rates and in an organization’s ability to plan, implement, monitor, and evaluate their campaign?

- 1. Research Objectives

1. To assess any changes in healthcare personnel immunization rates between the Control Group (usual campaign) and the Intervention Group (campaigns using the Guide)
2. To assess if, by tracking immunization rates by direct patient category, healthcare organizations are better able identify lower or higher immunization rates among the healthcare personnel who have the most direct patient contact (16)
3. To assess the effectiveness of the Guide. We will do this by assessing the Intervention Groups’ ability to make the changes in campaign planning, implementation, monitoring, and evaluation using the recommendations in the Guide
4. We will assess the delivery methods of the Guide (paper, web-based) and assess the Intervention Group’s satisfaction with ease of use, practicality of application, and need for outsider intervention
5. **Methods**
   1. Trial Design

This will be a multi-centre, cluster, randomized controlled trial.

2.2 Rationale for a Cluster Randomized Control Trial

Our intention in choosing a cluster randomized control trial design is to evaluate the impact of a tool designed for use at an organizational level, rather than an individual level. In order to understand its impact we will assess changes within each organization according to the research objectives detailed herein.

1. Participants & Study Setting

At least 46 healthcare organizations from across Canada will be selected to participate in the study.

The Guide is designed to be used across different types of healthcare organizations. Potential healthcare organizations will be self-identified, recommended by a project team member, and/or selected from the Canadian Healthcare Association’s Guide to Healthcare Facilities. Selected sites must meet the following eligibility criteria:

- - Canadian healthcare organizations who conduct seasonal influenza immunization campaigns
  - Have a systematic approach to collecting healthcare personnel immunization rates and be able to provide accurate and timely reports of immunization rates for categories of healthcare personnel
  - Agree to be randomized to receive the Guide or receive no intervention
  - If randomized to receive the Guide, the organization, including the campaign team and senior management, agrees to commit to adhere to the steps in the Guide to plan, implement, monitor and evaluate their campaign

Influenza immunization campaigns in healthcare organizations in Canada normally begin in October and end in December, with ongoing influenza immunization continuing outside of the reporting parameters until April.

1. **Interventions**

All organizations who agree to participate in the study will agree to provide their immunization rates for three years:

2008-2009 – Baseline Year

2010-2011 – Year One

2011-2012 – Year Two

We did not choose 2009-2010 as the baseline year because of the impact of pandemic H1N1.

- 1. Intervention Group

For the intervention group, there will be a Guide facilitator provided by the project team, normally the Project Manager or their delegate. The role of the Guide facilitator will be to provide basic information about the Guide and to facilitate the use of the web-based tools.

This Intervention Group will be invited to participate in either a half-day workshop or Webinar in September 2010 and September 2011. Ideally, this will be done in partnership with the Canadian Coalition on Immunization Awareness and Protection (CCIAP), public health and regional health authorities. The purpose of this intervention is to provide a basic introduction to the Guide and introduce the Guide Facilitator. The Intervention Group will be given access to the website and access to the Guide.

In March 2011 and again in March 2012, they will be asked to report their influenza immunization rates and complete an evaluation of the Guide.

In October, January and March of each campaign year, there will be a Webinar or Teleconference with the Intervention Group to answer questions, share challenges, and establish a community of practice. The Group, or subsets of the Intervention Group, may choose to meet more often and will be invited to participate in a web-based chat forum moderated by the Guide facilitator or their delegate.

- 1. Control Group

For the control group, the team will register the organization and will collect their immunization rates, baseline organizational data, and campaign activities for 2008-2009. We will contact them in March 2011 and March 2012 to collect immunization rate data and report on campaign activities. We will ask them open-ended questions to determine the content and process used in their more recent campaigns based on the focus group results from our work with the 16 organizations in 2009-2010.

They will be given access to the public part of the CHIIN website, and will be encouraged to calculate their immunization rates using the methodology in Appendix 3 of the Guide (16). This information will be publically available by September 2010.

The Control Group will be given access to the Guide at the end of the two-year period. In terms of contamination, Control Group participants may be disappointed and seek their own way of increasing immunization rates among healthcare personnel. The final unstructured interviews should capture this information.

- 1. Questionnaires

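### The eligibility criteria do not exclude organisations that piloted the Guide in 2009-2010, so a control site may already hold the intervention and pull the between-arm difference toward zero

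*Protocol*

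**What the plan says.** **Who may enter.** Under Participants & Study Setting: "Potential healthcare organizations will be self-identified, recommended by a project team member", and/or chosen from a national directory of facilities. The four criteria are running a seasonal campaign, systematic reporting of rates, consent to allocation ("Agree to be randomized to receive the Guide or receive no intervention"), and commitment to follow the Guide if allocated to it.

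**Who has used the Guide already.** Section 1.3 reports that in the 2009-2010 season "sixteen healthcare organizations agreed to use and evaluate the Guide". Of those who used it, the protocol gives "90% stating they made changes" to their campaign because of it.

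**The contrast.** The first research objective compares rates "between the Control Group (usual campaign) and the Intervention Group (campaigns using the Guide". The Interventions section fixes "2008-2009 – Baseline Year", and section 8.1 compares the arms by t-test on change from that year.

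**Safeguards.** The minimization factors are trial centre and organisation size. The Control Group text considers contamination only from controls that look for their own methods after allocation, and it delays their access to the Guide until the two years are over. It mentions the sixteen pilot organisations again only as a source for the control-group questions.

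**The concern.** The pilot season lies between the baseline season and Year One. If a pilot site is allocated to control, its change from 2008-2009 contains whatever the pilot achieved and the site has kept. That site no longer represents a usual campaign, and withholding the Guide from it for two years withholds something it already has.

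A pilot site allocated to the intervention shows the same pilot gain in its change score. Among earlier users, therefore, the difference between arms shrinks toward zero. A null result could not then separate an ineffective Guide from a control arm that was partly treated.

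Two of the three recruitment routes, self-identification and team recommendation, could readily bring in sites that already know the project team.

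**Working it through.** **1. The plan's own figure.** Inputs from the Sample Size section: ICC 0.05, 150 personnel per cluster, 46 clusters (23 per arm), 80% power, 5% significance. Two-sided testing is assumed. The control rate is not given there; section 1.2 reports averages of 40% to 60%.

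- Design effect: 1 + (150 − 1) × 0.05 = 8.45.
- The Kelsey formula at 45% vs 55% gives 393 per arm. 393 × 8.45 = 3,321, and 3,321 / 150 = 22.1, so 23 clusters per arm and 46 in total.
- At a 20-point difference (control rate 40% to 60%), the same approach, with or without continuity correction, gives only 10 to 14 clusters in total.

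The stated 46 clusters thus match a difference of about 10 points, although the section gives 20% without saying whether it is absolute or relative. Both sizes are carried forward.

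**2. Precision.** Effective number per arm: 23 × 150 / 8.45 = 408. At 50% vs 60%, SE = √[(0.50 × 0.50 + 0.60 × 0.40) / 408] = 0.0346. This is the precision of the sample-size model (a difference in rates), used as a planning approximation for the change-score test.

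**3. Dilution.** Let *k* of 23 controls be earlier Guide users that retain a share *c* of the effect *d*. Intervention sites are taken to show *d* in full whether or not they took part in the pilot. Expected difference = *d* × (1 − *c* × *k*/23).

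- *k* = 4, *c* = 1: 1 − 4/23 = 0.826, a 17% reduction.
- *k* = 8, *c* = 1: 1 − 8/23 = 0.652, a 35% reduction.

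*k* = 8 corresponds to all sixteen pilot organisations enrolling and splitting evenly.

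**4. Power** (noncentral t, 44 df, SE 0.0346):

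| True effect | Exposed controls | Carry-over | Expected difference | Power |
|---|---|---|---|---|
| 10 points | 0 | – | 10.0 | 81% |
| 10 points | 4 | full | 8.3 | 65% |
| 10 points | 8 | full | 6.5 | 45% |
| 10 points | 8 | half | 8.3 | 65% |
| 20 points | 8 | full | 13.0 | 96% |
| 20 points | 8 | half | 16.5 | over 99% |

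A two-proportion normal approximation with the same effective numbers gives 82%, 66% and 46% for the first three rows (45% control rate), and 97% for the 20-point row with full carry-over (50% control rate).

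**The case against.** **Nothing says a pilot site will enrol.** This is correct. The directory route reaches sites with no link to the team, and the promise of later access reads as if controls do not yet hold the Guide. The gap is a missing exclusion, not a stated plan to enrol treated sites. It remains a gap, because a pilot site that meets the four criteria is eligible.

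**Sixteen is a ceiling.** The protocol says that sixteen agreed to use the Guide, and the 90% refers to those who did. No count out of 16 rounds to 90% (14/16 = 87.5%, 15/16 = 93.8%), so fewer than sixteen may have reported back. Eight exposed controls is therefore an extreme case.

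**Full carry-over is generous.** Pilot sites had an earlier version, since updated, in a season disturbed by H1N1. As controls they would have no trial facilitator, workshops or webinars. The half carry-over rows allow for this.

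**Some information is collected.** Registration data, the March open-ended questions and the final interviews might reveal earlier use, and section 8.1 adjusts for baseline variables that differ significantly. But prior Guide use is not named anywhere in these provisions, and the March questions and final interviews come after allocation.

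**A stronger reading about the decision aid.** The Guide draws on "experiences of organizations implementing the OIDA in 2008-2009", which is the baseline season, and of the Guide the protocol says "It also introduces ways to incorporate the Ottawa Influenza Decision Aid". A reader might infer that such sites are also treated controls. The documents do not support that. The aid is described as a separate tool. Using it in the baseline year does not inflate a control's change score, and a raised baseline is balanced between arms in expectation. At most it leaves less room for improvement.

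**Conclusion.** The point holds for earlier users of the Guide. As written, the criteria allow up to sixteen pilot organisations into the trial, and each one allocated to control would weaken the contrast on which section 8.1 rests. The direction, toward zero, follows from the timing of the pilot, provided some of its effect lasted. The size cannot be derived: the number enrolled and the carry-over are both assumptions.

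The upper-bound loss is 17% of the effect with 4 exposed controls and 35% with 8. It would cost substantial power if the true effect is about 10 points and little if it is 20 points, but the estimate would be too small in both cases.

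Two further inferences should not be drawn: that pilot sites are known to be entering the trial, and that decision-aid sites need to be kept out.

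**What to change.** Add one criterion under Participants & Study Setting: the organisation has not received any earlier version of the Guide before randomisation. The cost is up to sixteen willing sites; they could go on using the Guide outside the trial.

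If those sites are needed to reach 46:

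- record prior Guide use for every organisation at registration, before allocation;
- add it to the minimization factors;
- prespecify an analysis restricted to unexposed organisations.

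Because prior use is fixed before randomisation, the restricted analysis keeps the randomised comparison. At worst it rests on 46 − 16 = 30 clusters. Minimization alone is not enough, since an even split still leaves exposed controls. It also requires the Randomization section to be reconciled, because the Randomization Type entry names simple randomization.

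Record prior use of the decision aid as a baseline characteristic, but do not make it an exclusion. The number of such sites is not stated, so the cost of excluding them is unknown, and the bias argument does not require it.

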**Control Group – September 2010**

- Registration Form
- Immunization rate data for 2008-2009

**Control Group – March 2011 and March 2012**

- Immunization rate data for each year
- Answer open-ended question re: campaign activities

**Intervention Group – September 2010**

The following questionnaires will be given before campaign begins:

- Registration Form
- Campaign Details Questionnaire
- Immunization rate data for 2008-2009

**Intervention Group – March 2011 and March 2012**

- Immunization rate data for each year
- Campaign Details Questionnaire
- Assessment of the Guide
- Assessment of the revised OIDA
- Assessment of the Toolkit

All questionnaires will be given as self-administered questionnaires and will be available online or via email. Each questionnaire will include check-box questions (which will be analyzed using descriptive analysis) and open-ended questions. The results from the open-ended questions and information gathered from the workshops, webinars, and teleconferences, plus interactions with the research team throughout the campaign season, will be summarized and synthesized in a post-campaign report each year.

1. **Study Outcomes**
   1. Primary Outcome

In the Intervention Group, a 10% improvement in healthcare personnel immunization rates from the base year (2008-2009) as compared to Year One (2010-2011) and Year Two (2011-2012)

This will be assessed by conducting a time-series analysis on how each organization does against themselves and between the Intervention and Control Group. In our systematic review of the effectiveness of influenza campaigns in healthcare organizations published in the Canadian Medical Association Journal (15) (see Appendix 2), methods for calculating change scores were used that enable comparisons across different types of studies randomized trials with only “after” assessments in the intervention and control groups as well as comparisons of studies that had change scores based on before and after the campaigns in control and intervention groups.

Also, we will assess the immunization rates against the benchmark of 90% set by the National Advisory Committee on Immunization (17).

- 1. Secondary Outcome

In both the Intervention and Control Group, we will assess improvement in the reporting of immunization rates, based on the methodology outlined in Appendix 3 of the Guide (16).

- 1. Tertiary Outcomes

Improvement in how each organization plans, implements, monitors, and evaluates their campaign will be observed. We will track this improvement comparing their campaign activities each year against the benchmarks established by the Checklist in the Guide.

Overall satisfaction with the Guide and with the delivery methods of the Guide, including preferences for web-based or paper tools, ease of use, practicality of application, and the need for outsider intervention, will be assessed.

1. **Sample Size**

The sample size is based on both the number of healthcare organizations and the number of healthcare personnel in each organization. We aim to accumulate data on a minimum of 150 healthcare personnel per cluster over 2 years. Thus, if an organization is in the trial for two years they will have to contribute at least 300 healthcare personnel to the trial. Note that we define a cluster as a healthcare organization. Sample size was calculated based on the equations of Kelsey et al. for Randomized Clinical Trial Studies (18) and multiplied by the design effect to get the number of subjects required for the cluster design. The level of difference between intervention organizations and the control organizations set in determining the sample size was 20%. This requires randomization and evaluation of immunization campaigns in 46 healthcare organizations (clusters) with 6000 healthcare personnel. Twenty-three will be randomized to the intervention group. With an intra-cluster correlation coefficient set at 0.05 and an average cluster size of 150 eligible healthcare personnel per healthcare organization, we will need a total of 46 clusters for 80% power and 5% significance.

- 1. Statistical Methods

As outlined in the sample size calculation for the study, the statistical analysis will be based on analyses using cluster analytic techniques.

- 1. Interim Analysis and Stopping Rules

We will conduct an interim analysis after completion of Year One. There are no stopping rules.

1. **Randomization**
   1. Randomization Sequence Generation

After organizations have declared their willingness to participate in the study, they will be randomized to be in the Intervention Group or Control Group. Due to the relatively small number of healthcare organizations in the trial, minimization will be used to allocate participants to intervention and control to ensure maximum balance. After all participants have been recruited, organizations will be individually allocated to an intervention and/or control group by the Ottawa coordinating centre using computer-generated random number tables, embedded in a computer program for minimization. The variables to be used in the minimization process will be trial centre (Ontario and Manitoba) and healthcare organization size (small, medium, large).

Organizations assigned to the control group will be informed that they will have access to the Guide at the completion of the study.

- 1. Randomization Type

Randomization will be performed using complete simple randomization.

1. **Statistical Methods**

The primary analysis will consist of comparing the Intervention Group with the Control Group. Characteristics of healthcare organizations will be compared descriptively at baseline. In order to adjust for the cluster design, we will calculate mean immunization rates and mean proportions of other characteristics for each healthcare organization to produce summary statistics.

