8.1 Primary Outcome

For Year One and Year Two, we will calculate the mean difference in immunization rates between the intervention year and baseline for both comparison groups. Assuming that the mean values are normally distributed within each group, we will use t-test to compare immunization rate difference means of the control group to the intervention group. We will consider *P* values < 0.05 to be significant.

Linear regression models will be used for continuous outcome variables (improvement in healthcare personnel immunization rates from the base year) and logistic models for binary outcome variables (attainment of the benchmark of 90% immunization rate set by the National Advisory Committee on Immunization). The assumptions for using each regression model will be checked and analyses adjusted accordingly. All analyses will be undertaken, adjusted for healthcare organization size, and for baseline variables which differ to a statistically significant extent between groups. Differential effects of the intervention by characteristics of healthcare organization and baseline rates will be assessed for the primary outcome measures by adding terms for the interaction between these characteristics and baseline rates and Intervention Group to the regression models.

Multilevel models will be applied to take account of clustering at the healthcare organization level and the Guide effects which will apply to differing extents in the intervention group (due to the effectiveness of campaigns in each participating healthcare organization). While the primary outcome will be attainment of the recommended benchmark of 90% set by the National Advisory Committee on Immunization, we will investigate the profile of immunization rate attainment at Baseline (2008-2009), Year One (2010-2011) and Year Two (2011-2012). This will be a repeated measures analysis. That is, evidence for differences in effect of the intervention at the different time points will be assessed.

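### The primary outcome is worded as a within-arm gain judged partly by a time-series on three annual rates, which conflicts with the valid between-arm analysis in Section 8

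*Protocol*

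**What the plan says.** In the Protocol, Study Outcomes, the primary outcome begins: "In the Intervention Group, a 10% improvement in healthcare personnel immunization rates from the base year (2008-2009". The sentence goes on to name Year One and Year Two as the comparison years. No control group appears in that definition. The method follows: "This will be assessed by conducting a time-series analysis on how each organization does against themselves and between the Intervention and Control Group".

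Section 2.2 uses similar within-organization language: "In order to understand its impact we will assess changes within each organization according to the research objectives detailed herein".

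Under Interventions, participating organizations "will agree to provide their immunization rates for three years". The first is labelled "2008-2009 – Baseline Year"; the others are 2010-2011 and 2011-2012. The gap is explained: "We did not choose 2009-2010 as the baseline year because of the impact of pandemic H1N1". The questionnaire lists ask for no other seasons' rates.

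Other parts of the protocol take a between-arm view. The Trial Design section says: "This will be a multi-centre, cluster, randomized controlled trial". Control organizations report rates for the same three seasons. The opening of Statistical Methods names the comparison of the two arms as the primary analysis. For each follow-up year, Section 8.1 states: "we will calculate the mean difference in immunization rates between the intervention year and baseline for both comparison groups". It then applies a t-test to those changes, control against intervention, and describes the three-year profile as repeated measures. No time-series method appears in Section 8.

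**The concern.** The outcome section fixes both a method and the data for it, and the two do not fit. A time-series of an organization against itself needs enough earlier points to show where its rate was heading. Here there is one. What remains is a before-after contrast with no control, running across a season that the protocol itself set aside as disturbed.

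The outcome definition has the same weakness at arm level. Read literally, a 10% rise in the Intervention Group meets it even if the controls rose just as much. The study would then have two rules for its primary outcome, one that uses the randomization and one that does not, and they can give opposite answers on the same data.

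**Working it through.** The protocol gives no figure on this point to reproduce. The check has three parts.

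**1. Can a single organization's series be modelled?** Put the seasons at t = 0 (2008-2009), 2 (2010-2011) and 3 (2011-2012). A series with a starting level, a prior slope, a step at the Guide and a change of slope has these rows:

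- t = 0: (1, 0, 0, 0)
- t = 2: (1, 2, 1, 0)
- t = 3: (1, 3, 1, 1)

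That is 4 parameters on 3 points, rank 3. A prior slope of b points a year gives the same fitted values as a step of 2b followed by a slope change of b: at t = 2 both give 2b, and at t = 3 both give 3b. For example, an organization already rising 2 points a year gains 4 and then 6 points. So does one with no prior trend, a step of 4 and a further 2. Three annual rates cannot tell them apart.

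**2. Can the two-arm comparison be modelled?** A model with arm, year and arm-by-year terms has 6 parameters for 6 arm-by-year means, rank 6, so it can be fitted. Let G be the Guide effect and s the change common to both arms. The change is G + s in the intervention arm and s in the control arm; the difference is G. Inside the intervention arm alone, only G + s is seen.

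**3. How much does the choice matter?**

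- From the protocol: 23 organizations randomized to intervention out of 46, hence 23 per arm; significance at P < 0.05.
- Assumed, because the protocol gives neither: a common shift of 0, ±5 or ±10 points, and an SD of organization-level change of 10 or 15 points.
- Guide effect set to zero; normal changes; 20,000 simulated trials per row; two-sided tests.

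| Common shift (points) | SD of change (points) | Before-after test, Intervention Group only: rejects | Between-arm t-test on changes: rejects |
|---|---|---|---|
| 0 | 10 | 5.1% | 5.0% |
| 0 | 15 | 4.9% | 5.1% |
| +5 | 10 | 63.4% | 5.0% |
| +5 | 15 | 33.6% | 5.0% |
| −5 | 10 | 62.4% | 5.2% |
| −5 | 15 | 33.4% | 4.8% |
| +10 | 10 | 99.6% | 4.9% |
| +10 | 15 | 86.6% | 5.0% |
| −10 | 10 | 99.5% | 4.9% |
| −10 | 15 | 86.2% | 5.0% |

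Hand check: the standard error of the arm's mean change is SD/√23, which is 10/4.80 = 2.09 or 15/4.80 = 3.13 points. A 5-point shift is therefore 5/2.09 = 2.4 or 5/3.13 = 1.6 standard errors from zero, in line with rejection in about two thirds and one third of trials.

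The 10% criterion can also be met without any Guide effect. If 10% means points, a common rise of 10 points takes the intervention arm's mean change to the criterion in about half of trials (49.8% at SD 10, 50.4% at SD 15). If it is relative, then at an assumed 50% baseline it is 0.10 × 50 = 5 points, and by symmetry a common rise of 5 points reaches it about half the time. The protocol does not say which is meant.

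**The case against.** The best defence is that time-series is only a loose label. The same sentence in Study Outcomes goes on to the comparison between groups, and the next one discusses change scores in intervention and control groups. Section 2.2 ties within-organization change to the research objectives, the first of which contrasts the two arms. Section 8.1 specifies a t-test on changes and calls the three-year profile repeated measures, and both can be computed from the rates collected. No passage proposes a segmented model. Omitting 2009-2010 is explained and applies to both arms.

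Most of this stands, and it rules out three stronger readings. A reader might infer that the control group plays no part in the assessment; the quoted sentence and Section 8 show that it does. A reader might infer that post-pandemic change will be credited to the Guide in the trial's main result; under the Section 8.1 t-test, change common to both arms cancels. A reader might also infer that each organization will be tested for change on its own and so count false calls across organizations; the protocol specifies no such test.

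The defence does not reach the outcome definition. That definition is a gain in one arm, and a lenient reading of time-series does not put a control group into it. Nor does Section 8 say that its comparison replaces the within-organization assessment. Because the protocol fixes both statements, this is a contradiction to resolve, not detail left for a later analysis plan.

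**Conclusion.** The point holds in this limited form: the primary outcome wording in Study Outcomes conflicts with the sound between-arm analysis in Section 8. The time-series of each organization against itself cannot estimate a prior trend from one earlier rate. The within-arm criterion cannot separate the Guide from change that would have happened anyway.

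That three annual rates give no prior trend, and that common change cancels between arms, follows from the design and needs no assumption. The size does rest on assumptions: with a common shift of 5 points and no Guide effect, the within-arm test rejects about 62-63% (SD of change 10 points) or 33-34% (SD 15) of the time, against about 5% for the between-arm test. Neither the shift nor the SD is in the protocol, and with no shift the two tests behave alike. The correction should be made, but the trial's design and its main analysis are not undermined.

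**What to change.** In Study Outcomes, delete the time-series and against-themselves wording. Restate the primary outcome as the difference between arms in organization-level change in immunization rate from 2008-2009, assessed by the comparison already set out in Statistical Methods and Section 8.1. Present within-organization changes and the 10% figure descriptively only, not as evidence of a Guide effect. Align the sentence in Section 2.2.

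Section 8.1 also names attainment of the 90% benchmark as the primary outcome. That is a separate matter, but the rewording should settle it so that only one definition remains.

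The cost is protocol wording: no new data, no change to sample size, and no new analysis. What is given up is any claim of a Guide effect from within-arm or single-organization change, which these data could not support.
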